## Abstract

**Background:**

Trauma is the leading cause of death and disability in children in the USA. Tranexamic acid (TXA) reduces the blood transfusion requirements in adults and children during surgery. Several studies have evaluated TXA in adults with hemorrhagic trauma, but no randomized controlled trials have occurred in children with trauma. We propose a Bayesian adaptive clinical trial to investigate TXA in children with brain and/or torso hemorrhagic trauma.

**Methods/design:**

We designed a double-blind, Bayesian adaptive clinical trial that will enroll up to 2000 patients. We extend the traditional *E*_*max*_ dose-response model to incorporate a hierarchical structure so multiple doses of TXA can be evaluated in different injury populations (isolated head injury, isolated torso injury, or both head and torso injury). Up to 3 doses of TXA (15 mg/kg, 30 mg/kg, and 45 mg/kg bolus doses) will be compared to placebo. Equal allocation between placebo, 15 mg/kg, and 30 mg/kg will be used for an initial period within each injury group. Depending on the dose-response curve, the 45 mg/kg arm may open in an injury group if there is a trend towards increasing efficacy based on the observed relationship using the data from the lower doses. Response-adaptive randomization allows each injury group to differ in allocation proportions of TXA so an optimal dose can be identified for each injury group. Frequent interim stopping periods are included to evaluate efficacy and futility. The statistical design is evaluated through extensive simulations to determine the operating characteristics in several plausible scenarios. This trial achieves adequate power in each injury group.

**Discussion:**

This trial design evaluating TXA in pediatric hemorrhagic trauma allows for three separate injury populations to be analyzed and compared within a single study framework. Individual conclusions regarding optimal dosing of TXA can be made within each injury group. Identifying the optimal dose of TXA, if any, for various injury types in childhood may reduce death and disability.

**Supplementary Information:**

The online version contains supplementary material available at 10.1186/s13063-021-05737-0.

## Background

Trauma is the leading cause of death and disability in children in the USA [1]. In the initial 24 h after injury, hemorrhage is the leading cause of death [2]. Tranexamic acid (TXA) is an antifibrinolytic lysine analog that blocks the conversion of plasminogen to plasmin thereby helping to attenuate bleeding. TXA reduces the blood transfusion requirements in adults and children during surgery [3–7]. The effectiveness of TXA in the surgical setting led to the Clinical Randomization of an Antifibrinolytic in Significant Hemorrhage (CRASH-2) and CRASH-3 trials, two separate international randomized controlled trials of early administration of TXA to adults with hemorrhagic torso trauma (CRASH-2) and hemorrhagic brain injuries (CRASH-3) [8, 9]. In CRASH-2, TXA reduce mortality with no increase in adverse events compared to placebo. In CRASH-3, patients randomized to TXA had lower mortality, but it was not statistically significant. In addition, a post hoc analysis of the CRASH-2 trial demonstrated improved functional outcomes associated with TXA use [10].

Several challenges exist for studying the efficacy of TXA in children. First, children are different from adults with regard to anatomy, physiology, and metabolism, all of which may affect the efficacy and safety profiles of TXA differently in children than it does in adults, creating uncertainty about the optimal dosing in children. Second, the efficacy and safety of TXA may be different in children with torso/abdominal hemorrhage than in children with brain hemorrhage, and children with both torso and brain hemorrhage (polytrauma) may also respond differently. Because severe hemorrhagic injury is less frequent in children than in adults, conducting separate clinical trials for each hemorrhagic condition in children (isolated brain, isolated torso, and polytrauma injuries) would be inefficient and costly. However, conducting a trial that combines all severe pediatric hemorrhagic injury groups in a single analysis could neglect important systematic differences in treatment effect that may exist between the groups. A pilot study enrolling 31 patients was successfully completed demonstrating the feasibility of patient consent, enrollment, and follow-up procedures [11], but a larger study is needed to assess efficacy.

Bayesian adaptive clinical trials have been successfully used to help study rare diseases and infrequent conditions [12, 13]. Adaptive designs allow for the features of the study to change in a pre-specified way based on accumulating data during the trial. These approaches are becoming more common, and the FDA has recently released guidance on adaptive designs in industry clinical trials [14].

The Traumatic Injury Clinical Trial Evaluating Tranexamic Acid in Children (TIC-TOC) trial is a Bayesian adaptive prospective, double-blinded, placebo-controlled, multicenter adaptive trial to assess the efficacy and safety of TXA in children with severe hemorrhagic injury to the brain and/or torso. The trial includes several innovative features designed to improve the efficiency of the trial and address inherent challenges. This trial will test the efficacy of at least two doses of TXA in children with hemorrhagic brain and/or torso injuries. The use of dose-response modeling and response-adaptive randomization allow efficient investigation of several doses, including a staggered approach to initiating the highest dose, which has been successfully performed in other studies [15, 16]. Additionally, we will incorporate a hierarchical model that leverages data across the injury groups for efficient estimation and inference. Finally, we propose a novel patient-centered endpoint that captures both the outcome and its trajectory.

## Methods/study design

The Traumatic Injury Clinical Trial Evaluating Tranexamic Acid in Children (TIC-TOC) study will be a multicenter trial in children with hemorrhagic brain and/or torso injuries. Study drug (TXA or placebo) will be given within 3 h of injury starting with a 30-min bolus dose followed by an 8-h infusion.

The trial will enroll up to 2000 children whose hemorrhagic injuries are classified as “Brain,” “Torso,” or “Both” at 30–40 academic level 1 trauma centers in the USA. The sample size will be adaptively determined by frequent interim analyses that will be performed after 500, 750, 1000, 1250, 1500, and 1750 patients are randomized. Initially, patients will be randomized equally among three study arms: placebo, TXA 15 mg/kg bolus dose then a 2 mg/kg/h infusion, and TXA 30 mg/kg bolus dose then a 4 mg/kg/h infusion, with the possibility of initiating a TXA 45 mg/kg bolus dose then a 6 mg/kg/h infusion arm later in the trial based on accumulating data. At each interim analysis, the randomization probabilities will be adjusted to preferentially allocate patients to better performing dosing arms, while the placebo arm probability will stay fixed. The trial will use a Bayesian hierarchical model that allows the estimates of the treatment effect for each of the injury types to be informed by the data accumulated from all injury types. SPIRIT reporting guidelines were used in this manuscript [17].

### Primary outcome measure: the Pediatric Quality of Life Inventory (PedsQL) area under the curve

The Pediatric Quality of Life Inventory (PedsQL) is a survey that assesses various quality aspects of a child’s life [18]. There are different versions based on a child’s age to account for development stages. The total score for all age versions ranges from 0 to 100 where higher scores correspond to a better quality of life, and the instrument has been validated across age groups. In the TIC-TOC study, the PedsQL survey will be administered 1 week, 1 month, 3 months, and 6 months after injury. The primary outcome in the TIC-TOC trial will be the area under the curve (AUC) of these surveys which results in a continuous outcome measure ranging between 0 and 100 [19]. AUC is commonly used for the analysis of longitudinal quality of life surveys and our approach to the derivation of AUC is similar to published literature [20, 21]. All four PedsQL measures (at the various time points) will be used in the calculation of the AUC for the Brain and the Both injury groups. Most patients with Torso injuries are expected to recover by one month, regardless of what treatment the patient receives. For this reason, in the Torso injury group, only the 1 week and 1 month surveys will be included in the primary outcome calculation. The AUC captures both the amount of recovery as well as the rate of recovery within a single measurement. It also allows a varying number of time points across injury groups to be incorporated into a single measure that is comparable across injury groups. The AUC may be calculated in the presence of missing follow-up visit surveys if the PedsQL is observed for at least one timepoint using the trapezoid rule. If only one follow-up PedsQL outcome is observed, that value is assigned to the AUC. For any single timepoint, a difference between PedsQL surveys of 4.5 units has been considered to represent a clinically meaningful difference [22]. We have applied this 4.5 clinically meaningful difference to the AUC outcome as well.

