### Response adaptive randomization

Response-adaptive randomization allows the proportion of patients allocated to the different dosage arms to change throughout the trial based on accumulating data. There are different methods and algorithms used to implement response-adaptive randomization; our method is similar to that described in Trippa et al. [26]. From the statistical model, we determine which dose is estimated to have at least 80% of the treatment effect (*ED*_80_) attributable to the maximum dose (i.e., 45 mg/kg). The randomization probabilities within each injury type will be proportional to the probability that each dose is the *ED*_80_ within that injury type. By targeting the *ED*_80_, the algorithm will tend to back away from the highest dose whenever a lower dose is available that maintains most of the treatment effect of the higher dose. This strategy helps minimize the number of children exposed unnecessarily to high doses.

Response-adaptive randomization is implemented starting after 500 total patients have been enrolled. After that, the proportions allocated to each arm within each injury are updated every time an additional 250 patients have been enrolled (i.e., after 500, 750, 1000, 1250, 1500, and 1750 patients). The allocation proportions across arms can differ between the injury groups. Only individuals who have an observed outcome will contribute to the response adaptive randomization. This means that recently randomized patients without an observed outcome will not contribute when the study reaches the interim sample size (e.g., 500), but will contribute their information to the following interim analysis assuming they have an observed outcome at that point. Because this study is conducted in a blinded fashion and study drug is given over 8 h, patients who were randomized to an arm that is suspended will have completed treatment by the time the allocations are updated and will not be notified of the suspension.

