### Simulations

To evaluate the behavior of the adaptive design, we performed computer simulations of the trial across a range of plausible scenarios. We created a set of hypothetical dose-response relationships for PedsQL AUC for each injury type. For each of the scenarios displayed in Fig. 1, we simulated 5000 trials. In each trial, we generated PedsQL AUC scores according to the truth for the scenario and had the computer conduct the design as specified above. This process was repeated, and the behavior of each “virtual trial” was tracked, including the number of patients assigned to each dose within each injury type, when accrual was stopped and the reason, and the selected dose, if any, for each injury type. These operating characteristics were then summarized across all simulated trials for each scenario.

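### The primary AUC is computed over whichever PedsQL visits exist, down to a single one, so children are scored on different time windows and dose comparisons can be biased

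*Protocol article*

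**What the plan says.** All of this is in the protocol article.

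- **Schedule** (section on the primary outcome measure): "the PedsQL survey will be administered 1 week, 1 month, 3 months, and 6 months after injury". Brain and Both use all four surveys. For Torso, "only the 1 week and 1 month surveys will be included in the primary outcome calculation".
- **Scale** (same section): the AUC is "a continuous outcome measure ranging between 0 and 100", so it must be a time-averaged score. The single-timepoint meaningful difference of 4.5 is carried over to it.
- **Missing visits** (same section): "The AUC may be calculated in the presence of missing follow-up visit surveys if the PedsQL is observed for at least one timepoint", by the trapezoid rule. For the extreme case, "If only one follow-up PedsQL outcome is observed, that value is assigned to the AUC". No minimum window is set, and nothing adjusts for which visits were seen.
- **Interim data** (Response adaptive randomization): "Only individuals who have an observed outcome will contribute to the response adaptive randomization". Whether one early survey makes an outcome observed is not stated.
- **Final analysis** (Stopping rules and decision boundaries): it waits until every child in that injury group has reached the last survey, and it also uses the data accumulated so far in the other groups.
- **Simulation** (Simulations): "we generated PedsQL AUC scores according to the truth for the scenario".

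**The concern.** PedsQL is expected to rise as children recover; for Torso the article says "Most patients with Torso injuries are expected to recover by one month". A time-average over a truncated window then estimates something other than the average over the scheduled window. A lone 1-week score takes the bottom of the curve and a lone 6-month score the top. A single score also cannot show the rate of recovery, which the article gives as a reason for choosing the AUC.

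This AUC feeds the one model behind the final conclusion, the allocation, the opening of 45 mg/kg and the stopping rules. If window length is related to dose, part of the estimated dose response reflects when children were measured. Two routes could create that link: visits missed at different rates by arm, and, at interims, visits not yet due in an arm that opened late.

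**Working it through.** **The plan's own figures.** The article gives no figure for the effect of partial windows. Its scenario 2 power (94.9% / 82.9% / 64.4%) cannot be reproduced, because the SD and priors are not in the article. What follows checks the scoring rule only.

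**Inputs.** From the article: survey times, the scoring rule, looks every 250 patients from 500, and 4.5 as the benchmark. Assumed: mean curves at 1 week / 1 / 3 / 6 months of 70-74-78-80 (10-point recovery), 60-68-76-80 (20) and 50-65-75-80 (30); uniform accrual of 250 patients in 3 to 12 months.

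**1. Weights, Brain and Both.** AUC = trapezoid area ÷ window length. At days 7, 30, 91 and 182 the window is 175 days:
- 1 week: (23/2)/175 = 6.6%
- 1 month: ((23+61)/2)/175 = 24.0%
- 3 months: ((61+91)/2)/175 = 43.4%
- 6 months: (91/2)/175 = 26.0%

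A 1-week-only child puts 100% on a visit worth 6.6%.

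**2. Shift for the same child under different visit patterns** (times in months, 1 week = 7/30.4). Full-window AUCs are 77.03, 74.05 and 72.23.

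| Surveys seen | 10-point | 20-point | 30-point |
|---|---|---|---|
| 1 week only | 70 − 77.03 = −7.0 | 60 − 74.05 = −14.1 | 50 − 72.23 = −22.2 |
| 1 week + 1 month | −5.0 | −10.1 | −14.7 |
| 1 week to 3 months | −2.1 | −4.3 | −5.7 |
| 6 months only | +3.0 | +6.0 | +7.8 |

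Torso: the full AUC is the mean of two scores, so a lone score is off by half the first-month gain: 4/2 = 2.0, 8/2 = 4.0, 15/2 = 7.5, downward for 1 week and upward for 1 month.

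**3. Final analysis, no true effect, Brain and Both.** Bias = (arm difference in the share of 1-week-only children) × shift.
- Equal patterns: 0.
- 5 percentage points: 0.05 × (−7.0 to −22.2) = −0.35 to −1.1.
- 10 percentage points: −0.7 to −2.2.

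**4. Interim, no true effect, if one survey suffices (Brain and Both).** Suppose 45 mg/kg opens at 500 and is assessed at 750, with T months per 250 patients. Its children have follow-up spread over 0 to T; placebo children over 0 to 3T. Example with T = 6 and the 20-point curve, among children with at least one survey:
- 45 mg/kg: 0.133×60 + 0.347×64 + 0.520×69.78 = 66.5
- placebo: 0.043×60 + 0.113×64 + 0.169×69.78 + 0.675×74.05 = 71.6
- difference: −5.1

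Over T = 12 to 3 months and the three curves the range is −1.2 to −9.5.

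**5. First look at 500, equal allocation.** There is no bias under the null or a constant effect. If the effect varies over follow-up, a true full-window difference of 4.5 would read 2.3 to 4.0 when the effect grows (profile 1, 2, 4, 6, rescaled) and 5.1 to 6.8 when it fades (8, 6, 4, 2, rescaled), for T = 3 to 12. The 45 mg/kg arm opens on a 4.5-unit threshold.

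**6. Sensitivity to end handling.** The article does not say whether, with two or more surveys, the last score is carried to the end of the window. If it were, 1 week + 1 month in step 2 becomes −3.3 / −6.6 / −8.2, and step 4 becomes −0.8 to −7.8. The single-visit shifts do not change.

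**The case against.** Four stronger readings are tempting, and the article does not support them.

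- **That the final comparison is biased outright.** The trial is double-blind, treatment is a bolus followed by an 8-hour infusion, and each group's final analysis waits for its own last survey. Missed visits produce null bias only if patterns differ by arm, and nothing in the article says they will. The 10-point imbalance is an illustration.
- **That a child with only a 1-week survey does enter the interims.** The article does not say so. A survey not yet due is arguably not missing, and the text holding back recently randomized children fits waiting for the complete outcome. If only closed windows count, steps 4 and 5 vanish. The Adaptive Design Report, not shown here, may settle this.
- **That the simulations drew one complete AUC per child.** The article says AUC scores were generated and the design then run as described. It neither confirms nor excludes partial follow-up.
- **That the Brain and Both weights apply throughout.** Torso has a 1-month window, so its shifts are smaller.

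The interim figures are also raw arm differences. Decisions use a monotone hierarchical model, the new arm is capped at 20% in its first period, and stopping starts only at 1000 patients. No effect on allocation or stopping probabilities was calculated. At 12 months per 250 patients, about half of the new arm already has a full window. The distortion in step 4 runs against the new dose, so that route does not point to false efficacy claims.

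What remains is the stated scoring rule. It puts children on different windows, and the 1-week-only shift exceeds 4.5 even on the mildest Brain and Both curve. Waiting for the last survey also does not fully protect a final analysis. Torso can close after 1 month of follow-up while Brain and Both children, whose data it borrows, are still within their 6 months.

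**Conclusion.** The point holds in conditional form. The rule scores children on different time windows; that follows from the text. Its size rests on assumed recovery curves: about 7 to 22 points low for 1-week-only and 3 to 8 high for 6-month-only children in Brain and Both, and 2 to 7.5 either way in Torso.

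At the final analysis the certain consequences are added noise and a changed estimand. Bias under the null needs arm-dependent missingness and is about 0.7 to 2.2 points per 10-percentage-point imbalance in 1-week-only children. At interims the raw deficit of about 1 to 9.5 points for a newly opened 45 mg/kg arm arises only if a partial AUC counts as observed, and it also depends on assumed accrual. A corrected power or sample size cannot be computed from the article.

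**What to change.** 1. Define the AUC over the full scheduled window of each injury group: 1 week to 6 months for Brain and Both, 1 week to 1 month for Torso.
2. Replace the single-value and truncated-trapezoid rule with a longitudinal model of the scheduled scores, or multiple imputation by injury group, arm, age and observed visits, and compute the AUC from its draws. If that model is right, the window shifts are zero by construction.
3. Define an observed outcome for interim use. Either apply the same model or include only children whose full window has closed. Apply this also when one group's final analysis borrows from groups still in follow-up.
4. Confirm that Table 2 was produced with partial and missing follow-up, or re-run it that way.
5. Add sensitivity analyses for missing visits that differ by arm.

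The cost is analysis-plan wording and possibly a simulation re-run. Data collection does not change. The downside is some model dependence, or fewer children contributing at interims if only closed windows count.

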### Statistical model

A dose-response model is used to characterize the relationship between the dose of TXA and outcomes as defined by the PedsQL AUC. The selected model is a hyperbolic *E*_*max*_ model [23], which is commonly used in dose-ranging studies in all stages of drug development [24]. The model has the distinguishing feature that it is monotonic; thus, higher doses are expected to have greater difference from placebo in average PedsQL AUC values.

The hyperbolic *E*_*max*_ model is typically used within a single population of interest. Since the TIC-TOC trial investigates three distinct, yet related, populations (Brain injury, Torso injury, and Both), we extend the model to accommodate multiple injury types. We introduce a hierarchical structure [25] to the model that allows inferences to be drawn within each injury group while leveraging data from all patients in the trial. This integration (“borrowing”) of information across injury groups is a key feature of the design and is especially critical for the Both injury group because the sample size is expected to be substantially smaller than for the other injury groups. The hierarchical model is specified a priori but the behavior of the model is dynamic in that it will borrow or share more information across injury groups when the observed effects of TXA compared to placebo are similar across injury groups, while the model results in less borrowing and more independent estimates when there is a more heterogeneous result observed. In addition, this borrowing reduces the overall probability of making at least one false claim of success under the scenario in which none of the injury groups has true benefit (the global null). When there is no effect of TXA in any injury group, the borrowing mitigates the impact of spurious results within a particular arm of an injury group. A benefit of the hierarchical model is a greater precision of estimates and better decisions regarding benefit of TXA in each injury type [25]. Details of the statistical model, including prior distributions, are provided in the supplement (Adaptive Design Report).

All inferences about the primary outcome will be based on this prespecified model, which will be periodically updated as described below using a Bayesian framework as data accrues during the trial. Probabilities derived from this model will guide all adaptive decisions within each injury type, including the response-adaptive randomization, the evaluation of pre-specified stopping rules, and whether to open a higher dose arm. The adaptive design rules are described below.

